## Chapter 15: Ancillary Studies

### 15.1 Risk of Re-emergence: Pediatric Longitudinal Study

We need a sample which can be followed longitudinally over time to determine how disease or infection re-emerges, and the value of multiple exposures to treatment. For this, a longitudinal sample of all children is needed. The sample for the trial is a simple cross sectional and thus the sample members may change at each round (as they age, or new residents move in, or as a consequence of sampling) this sample cannot address the critical questions of infection, trachoma, and re-emergence within children by number of years of mass treatment. For this, we propose a longitudinal cohort of children in a wider age range, for whom we can follow age and cohort effects. The second sample will consist of a longitudinal cohort of children ages nine and younger who will consist of all children in communities which are a sub-set of the randomly selected communities. For the longitudinal sample, we will randomly select up to three of the communities in each arm in which we will follow all children age 0 to 9 years at baseline. This sample will be a maximum of 750 children per arm, and a minimum of 300 children. Each year we will re-census the population of the communities to enroll any new children ages less than nine years. In this way, we can monitor the effect of treatment on successive age cohorts who have experienced variable numbers of rounds, and coverage, of treatment. They will also be followed up at each visit scheduled for the random sample, and exactly the same procedures for trachoma grading and ocular specimens will be used. For example, within each arm of the trial for Tanzania, we will have randomized 16 communities. Within each arm, at least one community will have all children ages less than 9 years followed longitudinally. These children will also serve as the random sample at baseline of children ages 0-5 years.

### 15.2 Modeling Trajectory of Disease Elimination: Public Health Planning Study

The optimal frequency, coverage, or duration of mass azithromycin distributions is unknown. While clinical trials are the gold standard to assess efficacy, they cannot explore all potential strategies for the different settings of interest. Mathematical models of infection transmission are a natural method to generalize the results of our specific trials. Here, we will use data from the proposal's clinical objectives to estimate region-specific transmission parameters for the mathematical model of trachoma. We will then use the model to determine the optimal frequency, coverage, and duration of treatment for different levels of endemicity.

### **15.3 Ancillary Benefits of Mass Treatment with Azithromycin**

As part of the larger PRET study, we will nest a study evaluating the added value of mass treatment on these other common morbidities. This ancillary study is not a randomized trial, because we could not randomize villages that met trachoma criteria not to receive azithromycin. However, in terms of other diseases, we do not expect differences in baseline prevalence. We intend to analyze the data at the village level to start.

The study would be conducted in Kongwa, Tanzania, in four communities already censused and slated to receive mass treatment with a single dose of azithromycin (Intervention communities). Four control communities would also be selected that did not have trachoma rates high enough to warrant mass treatment with azithromycin (mass drug administration or MDA). We plan to randomly select samples of children and adults in each of the eight villages for a series of cross sectional surveys and interim, bi-weekly, surveillance for six months.

### **15.4 Cost Effectiveness Study**

The cost effectiveness analysis will be based on community cost estimates that we will calculate using the cost collection instruments described below. For each community, we will collect cost information regarding: all medical and non-medical personnel involved in the study and all consumables used. We will also include laboratory costs attributable to screening/treating each community. The totality of the equipment costs - such as vehicles and field equipment costs – and laboratory costs will be recorded aggregately and then allocated to each community according to the community population. Further information on this ancillary study can be found in Chapter 9.

### **15.5 Laboratory Screening Study**

The laboratory screening study evaluates the utility of a trachoma laboratory screening for identifying “graduated” communities in Niger, Tanzania, and The Gambia.

## Chapter 16: Data Analyses Plan

---

### 16.1. Primary Outcome Analyses

The data analyses will address several key questions about mass treatment. The analysis will be performed on an “intention-to-treat” basis, according to the community’s original treatment assignment. In addition actual treatment compliance data for each community will be collected and used in the secondary analysis, which will allow us to directly model those communities where mass treatment was stopped. The main result of this study consists of two comparisons: one is between trachoma/infection prevalence in communities randomized to the two target coverage arms; the second between trachoma/infection prevalence in communities by either treatment frequency (yearly versus 6 monthly) or yearly versus according to the stopping rules for mass treatment. Initially, we will describe the comparability of the four intervention arms by comparing average community size, our key environmental variables, and baseline trachoma/infection. We will evaluate differences overall and among countries, as these differences can be incorporated as explanatory variables in the models.

To determine the changes in prevalence overtime we will conduct cross-sectional analyses of data for each of the follow-up visits: 6, 12, 18, 24, 30, and 36 months as well as longitudinal analysis incorporating the effect of time. The analysis will be carried out at two levels: first, using individual communities as the unit of analysis and second using the sentinel children as the unit of analysis and accounting by the clustering effect of children living in the same community.

These two approaches are complementary.

#### 16.1.1 Community-level Analysis

Cross-sectionally, trachoma/infection prevalence rates will be presented for each community and each time period stratified by randomization arm. We will test for differences in the mean prevalence rates between groups using a non-parametric approach: the Wilcoxon rank sum test when comparing two groups or its extension, the Kruskal-Wallis test when comparisons involve more than two groups.

To evaluate changes in prevalence over time, we will create mixed models with random effects using the logit of the prevalence of trachoma/infection as the outcome and allowing each community to have its own slope and intercept. As there is reason to believe that the two interventions may interact with each other, the possibility of an interaction effect should be

explored. The factorial design is optimally posed to test for such interaction. The models will take the following form:

$$\text{Log}\left(\frac{P_{it}}{1-P_{it}}\right) = (\alpha_0 + a_i) + (\beta_0 + b_i)t + \beta_1 x_{1i}t + \beta_2 x_{2i}t + \beta_{12} x_{1i}x_{2i}t + \gamma_{pi} + e_{it}$$

Where  $P_{it}$  is the prevalence of trachoma/infection for community  $i$  at time  $t$ ,  $x_{1i}$  and  $x_{2i}$  are indicator variables for the treatment assignment, high compliance with antibiotic treatment or treatment based on the stopping rule respectively.  $\alpha_0$  is the expected logit of the prevalence of trachoma/infection at baseline, which due to randomization is expected to be the same for the intervention groups. The deviations  $a_i$  of the prevalence of each of the communities from  $\alpha_0$  is handled in the model as a random effect.  $\beta_0$  is the fixed effect quantifying the expected decline of the prevalence of trachoma/infection with time on the study in the lower compliance without stopping rule group and  $b_i$  is the corresponding random effect allowing each community to vary from the overall rate of decline.  $\beta_1$ ,  $\beta_2$  and  $\beta_3$  are the parameters to test the null hypotheses of interest (i.e., the effect of interventions). All three parameters have the interpretation of accelerating the rate of decline of the prevalence of trachoma/infection. Specifically,  $\beta_1$  is the intervention effect for communities randomized to high antibiotic compliance only,  $\beta_2$  is the intervention effect in communities randomized to treatment based on the stopping rule, and  $(\beta_1 + \beta_2 + \beta_{12})$  for communities randomized to both high compliance and antibiotic treatment based on the stopping rule. Since at baseline there has not been any intervention and the groups are randomized, we do not expect any differences at baseline and thus the model should not include a main effect of the intervention groups. Were there to be a difference due to imperfect randomization, we would include a main effect. Furthermore, in the case that the interventions do not continuously depart from each other, we will categorize time instead of using it as a continuous variable. This model can be further extended to include additional variables ( $\gamma_{pi}$ ) to explore the effect ( $\gamma$ ) of environmental factors such as presence of water source, percentage of households with latrines, etc, on prevalence.

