#### **4.3.1 Details on Randomization for Niger**

Figure 1 illustrates the sampling plan for Niger. We will be working in the Matameye department of the Zinder Region. We will randomize at the grappe level.

For randomization, we stratified based on geography and endemicity. As indicated above, we began with six CSIs. Each of these six CSIs contributed 8 grappes to the study—with two grappes per CSI allocated to each of the 4 arms (for a total of twelve grappes in each of four arms, or 48 total). Moreover, we ranked the eight grappes from each CSI by clinical activity in 0-5 year old children. The top four of these were considered higher prevalence, and the lower four were considered lower prevalence. When randomizing, one higher prevalence grappe from each CSI was randomized to each treatment arm, and one lower prevalence grappe was randomized to each treatment arm. Finally, each study arm has one randomly chosen grappe intended for detailed longitudinal follow-up.

Each of the 48 grappes will have a complete census; the census will be used to randomly select children as well as provide the basis for data on treatment according to randomization into treatment arm. After the census, we will have a complete listing of all children five years or younger. One hundred of these children will be randomly selected, by assigning each child a random number and choosing the children 0-5 years associated with the lowest 100 numbers (or all children if a grappe has less than 100 in this age group). A second group of 20 children will be randomly selected as a substitution group if not all children from the first group of 100 are available. If a child on the list of 100 is not examined, the reason will be recorded (anticipated reasons include: moved to nearby grappe, moved to Maradi, Zinder, or Nigeria, absent for the day, absent more than 1 month, sick, or guardian refused). In addition, 40 adults (age 15+) will be randomly selected for monitoring at each collection.

[figure not shown]

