## 4.4 Sample Size

### 4.4.1 Villages

We estimated the sample size requirements for our two-by-two factorial design using simulation. Briefly, we generated simulated data assuming the alternative hypothesis and determined the sample size needed for how often (selecting 80%, our desired power) our statistical

test would yield a rejection of the null hypothesis. We adopt a non-inferiority design for each factor with non-inferiority limits of 8%. Assuming a standard deviation of 0.05 within each arm, a correlation of 0.5 between baseline and 36 month results (derived from previous studies), and no interaction between factors, we estimate that a total of 32 communities provides greater than 80% power for each main effect (95% one-sided non-inferiority). Thus, for Tanzania, out of a total of 32 villages, 16 villages will be assigned to annual treatment and 16 to a stoppage rule. We expect that between 40% and 80% of communities randomized to the stopping rule arm in The Gambia and Tanzania will stop mass treatment after one or two rounds, based on previous work. For Niger and the Gambia, the smaller community sizes imply a higher variance. Conservatively, we assumed the variance was one third higher. Thus, to obtain greater than 80% power, we require 12 villages in each arm (for a total of 48 villages, again assuming a one-sided 95% non-inferiority comparison with limit 0.08). Neither the assumption of plausible variation in the interaction effect nor the assumption of a beta distribution rather than a normal distribution alters these estimates to any substantial degree.

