### **1) What are differences at 3 years post baseline in rates of trachoma and ocular *Chlamydia trachomatis* in communities randomized to mass antibiotic coverage of low (80-89%) versus high ( $\geq 90\%$ ) coverage.**

*We hypothesize that higher coverage (as measured in ages <10 years) will result in lower prevalence of infection at three years in all countries.*

In principle, this could be addressed by a two-sample T-test. We estimate that the inclusion of 12 communities per arm in both The Gambia and Niger will provide greater than 80% power to detect a 6% difference in the prevalence of infection in individuals 0 to 5 years of age at 36 months, assuming a standard deviation of 5.0% and a two-tailed alpha of 0.05.

We computed the sample sizes for two-sample T-tests by finding solving the following standard equation for  $n$ :

---

 Snapinn SM. 2000. Noninferiority trials. Current Controlled Trials in Cardiovascular Medicine 1:19-21

$$\Psi_{2n-2}\left(t_{\alpha/2, 2n-2}, \frac{|\delta|\sqrt{n}}{\sigma\sqrt{2}}\right) = \beta \text{ (Chow et al, 2003)},$$

where sigma divided by the square root of n is the standard deviation (alpha=0.05), delta is the effect size, 1-beta is the power,  $\Psi_m(x, k)$  denotes the cumulative distribution function of the non-central T-distribution with m degrees of freedom and non-centrality parameter k, and  $t_{a,m}$  is the ath quantile of the T-distribution with m degrees of freedom and non-centrality parameter k, and  $t_{a,m}$  is the ath quantile of the T-distribution with m degrees of freedom.

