- We propose to compare chlamydia infection levels in adults (based on PCR taken from conjunctival swabs) at 36 months between the adult mass treatment arms and the children treated arms. The intent is to compare the herd effect (seen in the children treatment arms) with the direct effect. Specifically, we propose to use a linear model with 36 month adult prevalence as the outcome, baseline adult prevalence, and coverage as predictors.
- We propose to examine the final prevalence (36 month) prevalence in children in a linear model for all study arms. We will look at high vs low coverage, and biannual-

child vs annual-all age indicators as predictors (a factorial model). Baseline prevalence will be used as a covariate.

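### The planned analyses leave out Niger's 12 randomization blocks, test simple effects where the plan names main effects, and omit baseline from the community-level rank test

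*Protocol*

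**What the plan says.** **Randomization, Niger (4.3.1).** Each of six CSIs contributes eight grappes, split by clinical activity into a higher and a lower four. Then "one higher prevalence grappe from each CSI was randomized to each treatment arm, and one lower prevalence grappe was randomized to each treatment arm". That gives 6 x 2 = 12 blocks of four, "for a total of twelve grappes in each of four arms, or 48 total".

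**Sizing (4.4.1).** The simulation takes a baseline to 36-month correlation of 0.5 and no interaction, and concludes "we estimate that a total of 32 communities provides greater than 80% power for each main effect". The hypothesis-by-hypothesis t-test calculations use the per-cell numbers: 12 communities (Niger, The Gambia), "assuming a standard deviation of 5.0% and a two-tailed alpha of 0.05", and 8 (Tanzania) with a standard deviation of 4%, both for a 6-point difference.

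**Main result (16.1).** Two comparisons are named: one between the two coverage arms, the other between the two frequency or stopping-rule arms.

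**Community-level analysis (16.1.1).** At each survey the arms are compared by "the Wilcoxon rank sum test when comparing two groups or its extension, the Kruskal-Wallis test when comparisons involve more than two groups". Change over time uses a mixed model on the logit of prevalence with two 0/1 indicators and their product, each multiplied by time. The first indicator's coefficient "is the intervention effect for communities randomized to high antibiotic compliance only". The text lists beta1, beta2 and beta3 as the parameters for the hypotheses of interest, but the displayed model contains beta12 and no beta3.

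**Child-level analysis (16.1.2).** A logistic model with the same coding, adjusted for initial or previous community status.

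**Niger-specific analyses (16.2.4).** A 36-month factorial linear model of child prevalence on the coverage and frequency indicators: "Baseline prevalence will be used as a covariate". No CSI or block term is listed.

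**The concern.** A randomization that forces one grappe of every arm into each block takes between-block variation out of the treatment contrast. An analysis without the blocks leaves that variation in its error term, so the test is conservative and the interval too wide.

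The factorial coding matters in a different way. With 0/1 indicators and a product term, beta1 is the effect of high coverage among communities at the reference level of the other factor, estimated from half the communities. The stated main result is a comparison over all communities. Section 16.1.1 itself expects that the interventions may interact. If they do, beta1 and the main effect differ in meaning as well as in precision, and no section says which contrast of the fitted model is the main effect.

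Finally, section 1.3 has the primary analyses consider baseline prevalence, while the rank test under the primary outcome heading does not.

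**Working it through.** **1. The plan's own figures.** Two-sample t-test, two-sided 5%, non-centrality = difference x sqrt(n) / (SD x sqrt(2)).

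- n = 12, SD 5, difference 6: 6 x 3.464 / (5 x 1.414) = 2.94. Power is 80.2% (stated: above 80%), and 80% power needs n = 11.94 (stated 11.9).
- n = 8, SD 4, difference 6: 6 x 2.828 / (4 x 1.414) = 3.00. Power is 79.7% (stated: approximately 80%), and 80% power needs n = 8.06 (stated 8.06).

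Both reproduce. They compare one cell with one other cell.

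**2. Simple effect against main effect.** On the linear predictor, the effect of factor 1 is beta1 when factor 2 is at 0, and beta1 + beta12 when it is at 1. The main effect is their average, beta1 + beta12/2. With n communities per cell and common SD s:

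- Var(beta1) = 2s²/n
- Var(beta1 + beta12/2) = s²/n

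The ratio is 2, and sqrt(2) = 1.41. Adjusting for baseline at r = 0.5 multiplies the variance by 1 - 0.25 = 0.75. On the prevalence scale, in percentage points:

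| | Simple, no baseline | Main, no baseline | Main, baseline |
|---|---|---|---|
| SE, 12 per cell, SD 5 | 2.04 | 1.44 | 1.25 |
| SE, 8 per cell, SD 4 | 2.00 | 1.41 | 1.22 |
| 80%-detectable (2.80 x SE), 12 per cell | 5.7 | 4.0 | 3.5 |
| Power at 4 points, 12 per cell | 48% | 77% | 88% |
| Power at 6 points, 12 per cell | 82% | 98% | 99.7% |

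The 82% differs from 80.2% because the four-cell model has 44 residual degrees of freedom and the two-cell test has 22. Section 16.1.1 models logit slopes, so for its coefficients the table shows relative efficiency only.

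**3. Blocks in Niger.** The protocol gives no between-block share of the variance, so a range is assumed. Simulation: 20,000 trials, 12 blocks of four, normal outcome, total SD 5 points, two arms against two, no baseline adjustment.

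| Block share (assumed) | Type I error, unblocked rank test | Type I error, blocked analysis | Power at 4 points, unblocked | Power at 4 points, blocked |
|---|---|---|---|---|
| 0 | 4.8% | 5.1% | 75% | 77% |
| 10% | 4.1% | 5.2% | 76% | 81% |
| 25% | 2.8% | 5.2% | 78% | 87% |
| 50% | 0.9% | 4.8% | 82% | 97% |

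The prevalence half of the blocking is formed on baseline clinical activity, so these gains overlap with those from the baseline covariate and must not be added to them.

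**4. Baseline, section by section.** Section 1.3 names it for the primary analyses. The mixed model in 16.1.1 has it as the time-zero outcome. Sections 16.1.2 and 16.2.4 adjust for it. The rank test in 16.1.1 does not. For an interval on a mean difference at r = 0.5, leaving it out costs a factor 1/sqrt(0.75) = 1.155, about 15%. The rank test itself has no planned interval, so this figure only gauges the lost precision.

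**The case against.** The strongest reply is that little is lost. The two-group rank test can compare all communities by coverage or by frequency. The Niger linear model names the two factors and baseline and mentions no product term, so it gives main effects directly. The product-term model loses no information, because beta1 + beta12/2 is available from the same fit. Where interaction is expected, cell-specific effects are legitimate to report. Even a simple effect reaches the 6-point power target. Leaving out blocks makes the test conservative and creates no false positives, and the size of that loss rests on assumed shares. Stratification terms are also often left to a statistical analysis plan, which is not at hand.

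Most of this stands and limits the point. A reader might infer that the 36-month analyses ignore baseline altogether; sections 1.3, 16.1.2 and 16.2.4 show otherwise, and only the rank test is unadjusted. A reader might also infer that the research questions on coverage and frequency cannot be answered or that the trial is underpowered. The documents support neither.

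The deferral argument stands only in part. Chapter 16 is the protocol's own analysis plan, and 16.2.4 lists the Niger model's predictors without the blocks. Section 16.1.1 likewise names the coefficients to be tested, and none is a main effect.

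**Conclusion.** The point holds as one of efficiency and of naming the estimand.

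- **Blocks.** No planned analysis uses Niger's 12 blocks. The unblocked rank test runs at about 4.8% down to 0.9% for an assumed block share of 0 to 50%. At a share of zero almost nothing is lost, and part of any gain is already captured where baseline is in the model.
- **Coding.** The coefficients singled out in 16.1.1 and 16.1.2 are simple effects with twice the variance of the main effects named in 4.4.1 and 16.1. The factor of 2 assumes equal cells and equal variances.
- **Baseline.** The rank test is inconsistent with section 1.3 and with the other models.

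The per-cell power for a 6-point difference is correctly stated and is met. The results are not biased by these choices, and the direction of the error is conservative.

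**What to change.** Make the 36-month primary comparison in Niger and Tanzania a community-level model with both factors, baseline prevalence and the randomization strata: the 12 CSI-by-prevalence blocks in Niger, and the trachoma covariate used in the constrained randomization in Tanzania. Take each main effect from the additive model or from -1/2, +1/2 coding, which equals beta1 + beta12/2 under the present coding. Name that contrast as primary in 16.1.1 and 16.1.2 as well. Test the interaction separately as beta12 and remove the undefined beta3. The rank test can stay as a supporting analysis.

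The stated 6-point power figures need no change. Main-effect power may be given beside them: 98.3% for 24 against 24 at SD 5 (Niger) and 98.4% for 16 against 16 at SD 4 (Tanzania), both without baseline.

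The Gambia is left out, because section 4.3.3 assigns whole districts to cells and community-level strata do not address that.

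The cost is wording in Chapter 16 and 11 degrees of freedom in Niger: the additive model with baseline goes from 48 - 4 = 44 to 33. No data collection changes.

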### 16.1.2 Child-level Analysis

Using the sentinel children, we will construct for each period multivariate models with presence of active trachoma/infection as the outcome. Logistic models of the following form will be built to estimate the effect of the two treatments and their interaction:

$$\text{Log}\frac{\Pr(Y_i = 1)}{\Pr(Y_i = 0)} = \beta_0 + \beta_1 x_{1i} + \beta_2 x_{2i} + \beta_{12} x_{1i}x_{2i} + \gamma_{pi}$$

In this model,  $Y_i$  is an indicator variable for presence of trachoma/infection,  $x_{1i}$  and  $x_{2i}$  are indicator variables for the treatment assignment, high compliance with antibiotic treatment and treatment based on the stopping rule, respectively.  $\beta_1$  is the intervention effect for children living in communities randomized to high antibiotic compliance only,  $\beta_2$  is the intervention effect for children living in communities randomized to treatment based on the stopping rule, and  $(\beta_1 + \beta_2 + \beta_{12})$  for those living in communities randomized to both high compliance and antibiotic treatment based on the stopping rule. The models will include additional covariates ( $\gamma_{pi}$ ) to adjust for initial/previous period trachoma/infection status at community level and other factors thought to be related to the outcome that in spite of randomization were dissimilar at baseline. Because the

outcomes for children living in the same community are likely to be correlated, all standard errors will be corrected to account for that correlation using the Generalized Estimation Equation approach. Since GEE approaches work best when there are a large number of fairly small clusters, we will consider an alternative approach. Using communities as the cluster we will also implement a random effects model allowing the intercept  $\beta_0$  to be  $(\beta_0 + a_i)$  where  $a_i \sim N(0, \sigma^2)$  corresponding to the random variation of the  $i^{th}$  child in a given community. The models are easily implemented using PROC NLMIXED in SAS. We will compare the results of these two approaches to examine the consistency of the inferences.

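### In the longitudinal community model, adding arm main effects when a baseline imbalance is seen replaces baseline adjustment with change from baseline

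*Protocol*

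**What the plan says.** Section 16.1.1 sets up a mixed model for the logit of community prevalence. It has a random intercept and slope for each community, and treatment enters only through its product with time. The fixed intercept is defined as the expected logit at baseline, shared by all arms. The reason given is sound: "we do not expect any differences at baseline and thus the model should not include a main effect of the intervention groups". The following sentence sets the exception: "Were there to be a difference due to imperfect randomization, we would include a main effect". It gives no size, test or other criterion for a difference.

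The treatment-by-time coefficients are named as those that test the hypotheses of interest. Because the model contains an interaction term, the first of them "is the intervention effect for communities randomized to high antibiotic compliance only", so it contrasts one cell with one cell.

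Elsewhere the protocol keeps baseline in the analysis. Section 1.3 lists baseline prevalence among the co-variables for the primary analyses. Section 16.1.2 adjusts for initial or previous community status. The Niger 36-month factorial model in 16.2.4 includes baseline prevalence.

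**The concern.** With t = 0 denoting baseline, I read the baseline survey as one of the outcomes. A common intercept then makes this a constrained longitudinal model, which adjusts for baseline much as ANCOVA does. Adding arm main effects frees the baseline means, and the treatment-by-time terms then compare change from each arm's own baseline.

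After sound random allocation, an observed baseline gap is chance and is expected to shrink by itself. Change from baseline subtracts the whole gap, so the arm that started higher appears to improve more. The rule therefore gives up the adjustment in just those samples where it matters, and the choice of model depends on the data. At stake are the error rate and direction of the estimate in those samples, and some precision.

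**Working it through.** **Inputs.** Section 4.4.1 gives "Assuming a standard deviation of 0.05 within each arm, a correlation of 0.5 between baseline and 36 month results". The hypothesis-specific sizing there uses a 6-point difference, with SD 5% and 12 communities per arm (Niger, The Gambia) or SD 4% and 8 per arm (Tanzania), at two-sided alpha 0.05. My assumptions are equal SD at baseline and 36 months, normal community prevalences (the protocol's model is on the logit scale) and, where a trigger is needed, a baseline p<0.05.

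**1. The plan's own figure.** Two-sample non-central t, df = 2n−2, ncp = δ / (SD·√(2/n)).
- 12 per arm, SD 5%: ncp = 6/(5·√(2/12)) = 2.94, power 80.2%. The plan says "inclusion of 12 communities per arm in both The Gambia and Niger will provide greater than 80% power".
- 8 per arm, SD 4%: ncp = 6/(4·√(2/8)) = 3.00, power 79.7%. The plan says approximately 80%.

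The required n comes out at 11.94 and 8.06, matching the stated 11.9 and 8.06.

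**2. Variance of the 36-month contrast, two time points, relative to no adjustment.**
- Common baseline: 1−ρ² = 1−0.25 = 0.75.
- Own intercepts: 2(1−ρ) = 2×0.5 = 1.00.

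Power for 6 points, with one degree of freedom spent on the baseline adjustment:

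| Contrast | Own intercepts | Common baseline | Loss (points) |
|---|---|---|---|
| 12 v 12, SD 5% | 80.2% | 89.9% | 9.7 |
| 8 v 8, SD 4% | 79.7% | 89.2% | 9.6 |
| 24 v 24, SD 5% (pooled) | 98.3% | 99.7% | 1.4 |
| 16 v 16, SD 4% (pooled) | 98.4% | 99.7% | 1.3 |

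At 12 v 12 the loss is 17.5 points for ρ = 0.3 and 2.3 points for ρ = 0.7.

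**3. Conditional bias.** Given an observed baseline gap D, the gap expected to persist is ρD. Change from baseline removes D, which leaves ρD − D = −(1−ρ)D. At ρ = 0.5, a 2-point gap yields 1.0 point of spurious extra decline in the arm that started higher. With the common baseline the conditional bias is zero.

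**4. Error rate under the assumed trigger.** Simulated null trials, ρ = 0.5.
- Type I error given the trigger is 16-17% with t-tests and 18.5% with known variance. It is about 4-5% if baseline stays adjusted. Pooling does not remove this: it is about 17% at 16 v 16 and 24 v 24.
- The mean spurious effect given the trigger is about 2.2 points (8 v 8) and 2.3-2.4 points (12 v 12).
- Overall type I error of the two-stage rule is about 5.5-5.7%. A looser trigger (|z|>1) gives 6.3%. Averaged over gaps in both directions, bias is zero.
- For ρ from 0.3 to 0.7, the conditional error runs from 23% down to about 11-12%.

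**5. The printed form: linear time, random intercept and slope, seven visits.** The result depends on the covariance, which the protocol does not give. Over eight assumed structures with 12 per cell, the bias was −0.13 to −0.71 per unit of baseline gap with the main effects and zero without them. Where the main-effect version has 80% power for a cell contrast, the common-baseline version has 81% to 95%. In the three structures with a correlation of 0.46-0.52 it has 86% to 91%.

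**The case against.** Several points on the other side stand.

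- **Pooled comparisons barely suffer.** Section 4.4.1 claims power for each main effect, 16 v 16 villages in Tanzania, and 16.1 describes two main comparisons. A reader might infer that the trial loses 10 points of power. It does not: that loss belongs to single-cell contrasts at ρ = 0.5 with two time points.
- **The trigger is mine.** The sentence refers to imperfect randomization and could mean a failed allocation, not a chance gap. But no criterion separates the two, so the sentence can be applied to any observed difference.
- **Design protection.** Niger stratifies by health centre and by ranked clinical activity (4.3.1), and Tanzania uses constrained randomization on baseline trachoma (4.3.2). Large gaps are less likely than under the simple randomization simulated here.
- **The Gambia.** One whole district is assigned to each cell (4.3.3). A gap there may be a real district difference, so the regression argument is weaker and a forced common mean could itself cause bias.
- **Limited reach.** This model is introduced for change over time. The 36-month rank test is untouched, and other planned models adjust for baseline.

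A reader might also take 16.1.2 to use the same device, because it picks covariates such as "other factors thought to be related to the outcome that in spite of randomization were dissimilar at baseline". It always adjusts for community baseline status. Only the further factors are chosen by imbalance, so no baseline adjustment is removed.

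**Conclusion.** The point holds for the longitudinal community model in 16.1.1. The sentence is an unspecified, data-dependent switch that replaces a sound baseline adjustment with change from baseline when a chance imbalance appears. At ρ = 0.5 about half the gap then becomes apparent effect. With an assumed p<0.05 trigger, type I error in the triggered samples is about 16-18% instead of about 5%.

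Two stronger readings fail. The trial's error rate is not 16-18%: overall it is about 5.5-5.7%, because the trigger is rare. Nor do the documents show that the switch could by itself produce or hide an inferiority of the size of interest. The mean spurious effect of 2.2-2.4 points is well below the 6- and 8-point limits in 4.4.1, and nothing says that this logit-slope model tests non-inferiority.

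The sizes rest on ρ = 0.5, equal SDs, the assumed trigger and simple randomization. In the linear-time form they also depend on the covariance structure.

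**What to change.** **Niger and Tanzania.** Delete the sentence. State that the common-baseline form, without arm main effects, is kept whatever imbalance is observed, or that baseline prevalence is always a covariate, as 1.3 and the Niger 36-month model in 16.2.4 already provide. Show the own-intercept model as a sensitivity analysis only.

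**The Gambia.** Do not impose a common baseline mean. Name one model in advance, not by observed imbalance, and report the other as a sensitivity analysis.

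Section 16.1.2 needs no change on this ground. The cost is a few sentences of analysis wording, with no new data and no change to the sample size.
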